## Methods

### Study design

This study is a secondary IPD re-analysis of randomized controlled trials of antipsychotics in schizophrenia, schizoaffective or schizophreniform disorders. Item-level symptom ratings from the PANSS and BPRS will be collected and psychometrically analysed at baseline and outcome assessment. Reporting will follow STROBE
^
20
^ principles, and any deviations from the prespecified plan will be documented.

### Setting, participants and eligibility criteria

This study is open to randomized controlled multi-arm trials (Phase II-IV) comparing the effects of pharmacological treatments with antipsychotics to placebo (primary outcome) or any comparator (sensitivity analysis). Individual trial size is not an eligibility criterion. Eligible trials will include adult participants diagnosed with schizophrenia, schizoaffective or schizophreniform disorders. Trials must include PANSS and/or BPRS individual participant data at baseline and outcome. Studies meeting the criteria described in
Table 1 have been requested from
vivli.org (Vivli) and
yoda.yale.edu (YODA Project). Requested studies from the YODA Project are solely sponsored by Johnson & Johnson. In addition, Vivli provides data from the following sponsors: Abbott, AbbVie, Janssen, Johnson & Johnson, Lilly, Otsuka. Previous data checks suggests that we should expect to obtain a pooled sample of ~31 000 participants from 77 studies provided on the Vivli platform (
Table 2).

**Table 1. T1:** Inclusion/exclusion criteria for selecting trials and participant data.

Variable	Inclusion criteria
Study Type	Randomized controlled multi-arm trial
Data Type	Individual Participant Data
Phase	II, IIa, IIb, III, IIIa, IIIb, and IV
Population/Diagnostic Criteria	Participants with Schizophrenia Spectrum Disorders, aged 18 years and older
Treatment	Antipsychotic medication
Comparator	*Placebo* (to establish efficacy) *Active Comparator* (to establish baseline psychometric model)
Active Comparator	*Primary* (standard) *:* first-generation vs second-generation antipsychotics (optionally adding D2 partial agonists as a third category where feasible). *Exploratory:* receptor-based taxonomy as proposed by McCutcheon et al. ^ 21 ^
Outcome	Positive and Negative Syndrome Scale (PANSS) and/or Brief Psychiatric Rating Scale (BPRS)
Covariates	Sex (if available: Age)
Moderator Variable	Sex Stage of illness (sensitivity analysis)
Timing of Outcome Assessment	6 weeks, as per Younis et al. ^ 22 ^/ *4 weeks for sensitivity analysis*
	**Exclusion Criteria**
	All studies outside of the above parameters

**Table 2. T2:** Expected Sample.

Database One:		https://yoda.yale.edu/ (YODA Project)
Number of studies requested	-	62
Number of studies by sponsor		
*Janssen*	-	26
*Johnson & Johnson*	-	36

Database Two:		www.vivli.org (Vivli)
Number of studies requested	-	77 (62 are overlapping with YODA)
Number of studies by sponsor		
*Abbott*	-	1
*AbbVie*	-	1
*Lilly*	-	9
*Janssen*	-	26
*Johnson & Johnson*	-	36
*Otsuka Pharmaceuticals*	-	4

### Outcome measures
*:* PANSS and BPRS

The PANSS
^
1
^ is one of the most widely used clinician-rated outcome measures in schizophrenia research. It comprises 30 items, each rated on a 7-point anchored severity scale (1 = absent to 7 = extreme), which is commonly summarised as three symptom groupings: Positive (7 items), Negative (7 items), and General Psychopathology (16 items), together forming a total score ranging from 30 to 210. Despite its extensive use, heterogeneity in reported factor solutions and item functioning has prompted concerns about the PANSS’ psychometric robustness and its sensitivity to treatment-related change under some conditions.
^
6
^
^,^
^
23
^

The BPRS is another long-established clinician-rated scale frequently used in psychopharmacology research to quantify a broad range of psychiatric symptoms (e.g., thought disturbance, affective symptoms, activation, hostility).
^
2,
24
^ We will utilize the BPRS version comprising 18 items, each rated on a 7-point severity scale (1 = not present to 7 = extremely severe), producing total scores that typically range from 18 to 126. As with PANSS, published work indicates that factor structures and item performance can vary across samples and settings, which is relevant when BPRS totals are used as trial outcomes.
^
7,
8,
25,
26
^

### Statistical analysis plan

Analyses will be conducted within the secured environment of Vivli. Our approach will follow a two-stage workflow. First, we will use item-level PANSS and BPRS data to evaluate and select the best-fitting, state-of-the-art psychometric models of symptoms. Second, we will use the resulting psychometrically-informed scores to estimate antipsychotic treatment effects and compare these with effects derived from conventional PANSS/BPRS total scores, thereby quantifying whether and how psychometric modelling alters trial-level and pooled treatment effect estimates. We will follow a similar methodological approach as detailed in the publications provided by Doyle et al.,
^
19
^ regarding the exploratory and confirmatory factor analyses (EFA, CFA) and Byrne et al.,
^
11,
13,
15
^ regarding the item response theory framework (IRT) and network analytical approach (NA).

### Stage 1: Establishing optimal psychometric models of PANSS and BPRS

### Exploratory and Factor analytic approaches

Data will be randomly split into exploratory and confirmatory datasets, as recommended by Lubke and Luningham,
^
27
^ with stratification by treatment group and trial to ensure balanced representation. For stratification and subsequent subgroup/invariance checks, active antipsychotic arms will be coded using literature-standard classification (primary approach: first-generation vs second-generation antipsychotics; where feasible, a third category for D2 partial agonists may be considered). In exploratory analyses, we will additionally code active agents using McCutcheon and colleagues’ data-driven receptor-based taxonomy,
^
21
^ namely muscarinic (M2-M5) receptor antagonists; dopamine (D2) partial agonists and adrenergic antagonists; serotonergic and dopaminergic antagonists; and dopaminergic antagonists. We will ascertain factor models of schizophrenia for baseline (pre-treatment), combined outcome (post-treatment; 6 weeks) and separately for placebo and treatment groups. We will further evaluate measurement invariance across major arm categories (e.g., placebo vs active treatment and, where supported, across active treatment-arm classes) within the best-fitting baseline model(s).

Parallel analysis will be applied to the exploratory datasets to determine symptom dimensionality.
^
28
^ Next, the EFA will be performed, using oblique rotation to allow for correlated symptom domains, to examine the factor structure of the exploratory dataset. Models will be refined iteratively by evaluating factor loadings below 0.3 and/or communalities below 0.4, with poorly performing items removed where justified to achieve stable and interpretable solutions.
^
29
^

In the confirmatory dataset, CFA will be used to formally test candidate psychometric models identified during the exploratory phase. In addition to simple structures derived from EFA, established alternative models, including higher-order and bifactor representations, will be evaluated.
^
30
^ To select the optimal model of schizophrenia, the selection process will be guided by established absolute and relative fit indices, information criteria, and internal consistency metrics, including: the Root Mean Square Error of Approximation (RMSEA; < 0.08), Standardised Root Mean Square Residual (SRMR; < 0.08), Comparative Fit Index (CFI; > 0.95), Tucker-Lewis Index (TLI; > 0.95), Akaike Information Criterion (AIC), Bayesian Information Criterion (BIC), and McDonald’s Omega (acceptable >0.70), following established practices.
^
31,
32
^ Similar to the exploratory approach, confirmatory modelling will be performed for baseline and for the primary post-baseline outcomes. For outcome (post-baseline) measurement models, we will estimate the best-fitting model in the pooled sample and then test invariance across key arm categories (placebo vs active; and where feasible across active-arm classes as defined by the standard classification, with McCutcheon’s taxonomy explored in sensitivity analyses). We will retain the best-fitting baseline and post-baseline model(s) to derive factor scores for downstream treatment-effect estimation in Stage 2.
^
33
^

Measurement invariance, i.e. metric invariance (factor loadings are equal) and scalar invariance (intercepts are equal) across sex will be assessed, and differential item functioning examined by mean, standard error, standard deviation, factor loading scores and
*r
^2^
* values. When invariance is violated, psychometrically optimized models will be examined separated by sub-group (e.g., women and men).

The outcomes of these analyses will then be used for further evaluation and discussion (descriptively) on their differences or similarities in all models and datasets. This procedure will include model structure or item functioning (i.e. dropped items, item loadings on factor). Revised sum scores based on the retained items and weighted scores will then be computed from the best performing baseline and combined outcome model for each measure. These will be used for the stage 2 analysis described in the following sections.

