### Item response theory approaches

Similar to the procedure described above, we will also use IRT approaches.
^
34,
35
^ In IRT, each item is treated as providing information about a latent trait, and items are evaluated by how strongly they discriminate between individuals at different levels of that trait (i.e., higher latent severity increases the probability of endorsing higher response categories). Within an exploratory dataset, we will use non-parametric IRT (Mokken scaling) to assess scalability, dimensionality, and item ordering, and to identify poorly discriminating items. Following recommendations by Meijer and Baneke,
^
36
^ we will evaluate solutions across increasing lower-bound scalability thresholds (c), beginning at c = 0.01 and then stepping by 0.05 (i.e., 0.05, 0.10, 0.15 … up to 0.60), selecting the most interpretable solution. Second, using the confirmatory dataset, we will fit parametric IRT graded response models to estimate item parameters (e.g. discrimination and category thresholds) to identify the best fitting model. Hence, we will compute revised sum scores based on the retained items and generate latent trait (weighted) scores for use in downstream analyses within stage 2.
^
37
^ A detailed description of the analysis principles for the IRT approach is outlined in Byrne’s publications.
^
11,
13
^

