### Network analytic approaches

Network analysis is a more recent approach to psychometrics, which differs from traditional theories in that it does not assume that symptoms are caused by a single underlying latent trait. Instead, NA conceptualises symptoms as mutually interacting components, represented as a graph in which nodes are symptoms and edges reflect conditional associations between symptoms.
^
38,
39
^ This perspective has been proposed as a clinically intuitive complement to traditional models of psychopathology. Using best practice approaches, we will estimate empirical network structures separately for baseline (pooled across arms) and outcome data (separated by treatment arm). Network analysis will follow an exploratory graphical workflow, to identify the dimensional structure and detect redundant or weakly-performing items. As recommended by Christensen and Golino,
^
40
^ bootstrap-based stability assessment will be applied and empirical networks will be assessed in relation to the bootstrapped samples. Their work also suggests that replication metrics around the ~0.65–0.75 range mark the point at which variables begin to show reduced stability, providing a practical basis for identifying potentially unstable items.
^
12,
40
^ A key goal is to identify a network structure that is stable and configurally invariant across baseline and outcome (or treatment arms). If invariance cannot be achieved, we will proceed with the network solution with fewest/least consequential instabilities. From the final network solution, we will compute (i) revised sum scores based on the retained items, and (ii) weighted “net scores” derived from network loadings/strength. A detailed description of the analysis principles for the NA approach is outlined in Byrne’s publication.
^
15
^

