In this context, psychometric re-modelling using pooled IPD may help clarify which symptom structures replicate reliably, which items contribute meaningfully, and whether abbreviated scales will capture the same responsiveness to treatment or whether weighted scoring yields more accurate estimates of change. Importantly, we do not claim that psychometric refinement necessarily produces clinically meaningful change at the individual level. Rather, the planned analysis evaluates whether relatively modest differences in effect size (e.g., ~10–15% as observed in prior IPD psychometric work) are detectable and may improve the precision, interpretability, or comparability of trial effect estimates. Yet, they can still matter for meta-analytic synthesis, trial power, and the likelihood of detecting true treatment differences under challenging conditions.

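### The confirmatory dataset contains the same trials as the exploratory one, so Stage 1 cannot show whether a PANSS or BPRS structure holds across trials; a leave-trials-out check should be added

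*Protocol article*

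**What the plan says.** Under Exploratory and Factor analytic approaches, the article states: "Data will be randomly split into exploratory and confirmatory datasets", "with stratification by treatment group and trial to ensure balanced representation". No split ratio is given. The second set then carries the confirmation: "In the confirmatory dataset, CFA will be used to formally test candidate psychometric models identified during the exploratory phase". The section on item response theory follows the same logic: "using the confirmatory dataset, we will fit parametric IRT graded response models". Retained items and weights from these steps become the Stage 2 scores (Models 2a, 2b, 3a and 3b).

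Invariance is planned for other groupings. For post-baseline models, "we will estimate the best-fitting model in the pooled sample and then test invariance across key arm categories". For sex, "metric invariance (factor loadings are equal) and scalar invariance (intercepts are equal) across sex will be assessed". The network section looks for a structure that is stable between baseline and outcome or between arms. Trial is never a grouping factor in Stage 1, and random intercepts for trial appear only in Stage 2.

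The article also says, under Outcome measures, that published factor structures and item performance can differ by sample and setting. Under Limitations it says that differences in the available trial data may affect the psychometric models. The Discussion says that the pooled modelling may help clarify "which symptom structures replicate reliably".

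**The concern.** A confirmation step is informative only about sources of variation that differ between the two datasets. When the split is made within trial, whatever is peculiar to the mix of trials is present on both sides and cancels in the comparison. An item whose home factor changes from trial to trial has some net leaning in this particular collection. That leaning tends to appear in both sets, so the second set seems to confirm it.

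At stake is what may be said about the Stage 1 structures. Without evidence from trials that played no part in deriving a structure, the study can neither support nor limit a statement about which structures replicate. Nor can it say how far the scoring keys would carry over to a new trial.

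**Working it through.** **Inputs.** From the article: 77 trials and about 31,000 participants, so 31,000/77 ≈ 403 per trial; random split stratified by trial and arm. Assumed, because the article gives no value: an equal split, the between-trial SD τ of the parameter concerned, and a mean inter-item correlation of 0.30 in step 1.

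**1. What the split can see.** Let a parameter in trial k be θ + u_k with SD(u_k) = τ, N participants in all and K trials.

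- Split within trials: Var(exploratory − confirmatory) = 4σ²/N. There is no τ term.
- Split by whole trials: about 4σ²/N + 4τ²/K.
- Error when carried to a new trial: about τ²(1 + 1/K), plus sampling error 2σ²/N.

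For a correlation of 0.30, σ ≈ 1 − 0.30² = 0.91. The first SD is 2 × 0.91/√31,000 = 0.0103, whatever τ is. At τ = 0.10 the second is √(0.0103² + 4 × 0.01/77) = 0.025. Simulation with 77 trials of 402 participants gave:

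| τ | SD of difference, planned split | SD of difference, whole-trial split | SD of error to a new trial |
|---|---|---|---|
| 0 | 0.0105 | 0.0105 | 0.007 |
| 0.05 | 0.0100 | 0.0154 | 0.048 |
| 0.10 | 0.0106 | 0.0238 | 0.100 |
| 0.20 | 0.0097 | 0.0468 | 0.207 |

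The planned comparison stays at about 0.010 while the error to a new trial grows about thirty-fold (0.207/0.007 ≈ 30).

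**2. What this does to item assignment.** Take an item whose two loadings differ by zero on average, with between-trial SD τ for that difference. Simulations and an approximation with 77 unequal trials and 31,000 participants gave these rates of agreement between the two sets on the item's dominant factor:

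| τ of loading difference | Planned split |
|---|---|
| 0 | 50% |
| 0.05 | 56-57% |
| 0.1 | 63-66% |
| 0.2 | 78-81% |
| 0.3 | 84-86% |
| 0.4 | 87-91% |

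Holding out whole trials gave 47-51% at τ = 0.2 to 0.4, which is chance.

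**3. Closed-form check with equal trial sizes.** The simulated set-to-set SD of the loading difference under the planned split is about 0.0235, so each set has error variance 0.0235²/2 = 0.000276. The shared trial-mix variance is τ²/77. With ρ = (τ²/77)/(τ²/77 + 0.000276), agreement is 1/2 + arcsin(ρ)/π.

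- τ = 0.05: ρ = 0.105, agreement 53%.
- τ = 0.1: ρ = 0.320, agreement 60%.
- τ = 0.2: ρ = 0.653, agreement 73%.
- τ = 0.4: ρ = 0.883, agreement 84%.

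Unequal trial sizes lower the effective number of trials, which is why the table in step 2 is higher. The direction is the same.

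**4. Does another planned analysis fill the gap?** The Stage 2 trial-level analyses compare SMDs from scores already fixed and do not re-test the structure. Repository-specific reporting is no hold-out: Table 2 lists 62 YODA studies (26 + 36), all among the 77 in Vivli, leaving only 77 − 62 = 15 outside the overlap. Established alternative models are fitted to the same trials. Comparisons by drug class, illness stage and endpoint timing bear on some differences between trials, but they are conditional on feasibility and leave no trial out of the derivation.

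**The case against.** The strongest reply is that the split does what it was chosen for. Its stated purpose is balance, it protects against participant-level overfitting, and none of the three objectives is external replication. All of that stands. The pooled 31,000 also spans both scales, and models are fitted separately by placebo and treatment group and, where invariance fails, by sex. Single analyses may therefore be much smaller than half the total, and participant-level error is not negligible everywhere.

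Four stronger readings are tempting, and the article does not support them.

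- A reader might infer that the protocol treats between-trial heterogeneity as its main threat and promises replication. It lists heterogeneity among several limitations, in conditional wording, and the Discussion says only that the work may help clarify replication.
- A reader might take the 78-91% as the rate at which the protocol would confirm a spurious assignment. It is not. The plan screens items on loadings and communalities and judges CFA models by CFI and TLI above 0.95 and RMSEA and SRMR below 0.08, against higher-order and bifactor rivals. When a simple-structure CFA was fitted with three near-equal cross-loading items (assumed loadings, 18 settings), CFI was 0.82-0.948 and TLI 0.79-0.94, below those guide values. In the simulations, all three such items agreed together in only 52-77% of runs, so the planned split flagged at least one in 23-48%.
- A reader might extend the criticism to the networks, where "bootstrap-based stability assessment will be applied and empirical networks will be assessed in relation to the bootstrapped samples". The article does not name the resampling unit and refers to a publication for detail, so no error can be asserted.
- A reader might conclude that the primary SMD difference is biased. Stage 2 applies the scores to these same trials, and no such bias has been shown.

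Nor would a whole-trial split cure every artefact. A mean shift shared by items within a trial produces a spurious first factor under either kind of split; that is a question of centring.

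**Conclusion.** The concern holds as a limit on what the confirmation step can show. Stratifying by trial removes between-trial variation from the exploratory-confirmatory comparison, and no other planned analysis tests a structure on trials that did not help derive it. This follows from the stated design and does not depend on the split ratio.

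The size is uncertain because the article gives no between-trial SD. With an SD of 0.05, spurious agreement is only slightly above chance; at 0.2 or more it is substantial; at zero it vanishes. The harm is to statements about replication and to use of the scoring keys beyond these trials. It is an inexpensive improvement to the plan and does not invalidate the primary analysis.

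**What to change.** Keep the present split and add an internal-external check to Stage 1. Divide the trials into groups. Leave each group out in turn, derive the item set and scoring key on the remaining trials, and apply them to the trials left out. Report model fit, item retention and item assignment in those trials. Describe a structure as replicating only on that evidence, and describe the existing confirmatory step as a check on participant-level overfitting.

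Replacing the split by one that assigns whole trials would also respond to between-trial variation, but it gives up some balance between the sets, so the added check is the easier change.

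The cost is protocol wording and computing time. No new data are needed. The replication figures may turn out less favourable.

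### The arm-invariance tests are specified in the pooled sample, with no restriction to trials that randomised the contrast and no conditioning on trial, so arm is partly confounded with trial population

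*Protocol article*

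**What the plan says.** The section on setting and eligibility admits trials that compare antipsychotics "to placebo (primary outcome) or any comparator (sensitivity analysis"). Table 1 gives active-comparator data a role in Stage 1: "to establish baseline psychometric model". The expected total is about 31,000 participants "from 77 studies provided on the Vivli platform".

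The Stage 1 section on exploratory and factor-analytic approaches describes two arm comparisons. One is an evaluation of "measurement invariance across major arm categories (e.g., placebo vs active treatment and, where supported, across active treatment-arm classes) within the best-fitting baseline model(s"). The other concerns week 6: "we will estimate the best-fitting model in the pooled sample and then test invariance across key arm categories", again placebo against active and, where feasible, the active classes.

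In Stage 1, trial is mentioned only as a stratum, with treatment group, for the split into exploratory and confirmatory halves. A random intercept for trial appears only in the Stage 2 outcome models. Neither invariance statement limits the test to trials that randomised the contrast or conditions it on trial.

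**The concern.** Invariance between arms at week 6 supports reading a drug-placebo difference on a factor score as a difference in symptoms rather than in how items behave under treatment. That support comes from randomisation, which holds within trials.

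In a pool of placebo-controlled and active-comparator trials, the placebo group comes only from the first kind and the active group from both. If items behave differently between the two kinds of trial, that difference enters the placebo-active contrast. The test can then fail although treatment leaves measurement unchanged, or pass because trial mix offsets a real effect. The active-class comparison has the same weakness unless the classes were randomised against each other within a trial.

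At stake is the interpretation of the factor-score models (3a and 6a). Stratifying the split by trial and treatment group makes the two halves alike. It does not make the arms alike within a half.

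**Working it through.** The article states no sample size, power or error rate for the invariance tests, so there is no figure of the plan's to reproduce. As a check on the pool, the Vivli sponsor counts in Table 2 sum correctly: 1 + 1 + 9 + 26 + 36 + 4 = 77.

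**Structure.** Let T be the shift in an item intercept caused by treatment, f the share of active participants from trials without placebo, and D the intercept gap between the two kinds of trial, in item SDs.

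- Apparent week-6 gap = T + f × D
- Apparent baseline gap = f × D (no treatment yet)

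The document gives neither f nor D. With T = 0 and D = 0.2, the week-6 gap is 0.05, 0.10 and 0.15 for f = 0.25, 0.50 and 0.75. Over D = 0.1 to 0.3 and the same f, it runs from 0.025 to 0.225. At f = 0 this component vanishes. A pass can also mislead: T = 0.1, D = −0.2 and f = 0.5 give 0.1 − 0.1 = 0.

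**Size if trials vary at random.** From the document: 31,000 participants and 77 trials, so 31,000 / 77 ≈ 403 per trial if equal. Assumed: equal trial sizes, K = 15 to 35 placebo-controlled trials, 2:1 allocation, a 50:50 split (no ratio is stated), and between-trial SD τ of an item intercept = 0.2 item SDs.

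- f = active participants in trials without placebo / all active participants
- Trial-mix SD = f × τ × √(1/(77 − K) + 1/K)
- Sampling SE = √(1/n_placebo + 1/n_active)

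| Confirmatory half, τ = 0.2 | K = 15 | K = 35 |
|---|---|---|
| Placebo participants | 1,006 | 2,348 |
| Active, placebo-controlled trials | 2,013 | 4,697 |
| Active, other trials | 12,481 | 8,455 |
| f | 0.86 | 0.64 |
| Trial-mix SD | 0.050 | 0.029 |
| Sampling SE | 0.033 | 0.022 |
| Ratio | 1.5 | 1.3 |

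For K = 15: 0.861 × 0.2 × √(1/62 + 1/15) = 0.050, and √(1/1,006 + 1/14,494) = 0.033. For τ = 0.1 to 0.3 the ratio runs from about 0.7 to 2.3. Using all 31,000 participants without the split would give 1.9 to 2.2 at τ = 0.2, but the article places the CFA in the confirmatory half.

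A ratio r turns a two-sided 5% test into one that rejects with probability 2 × [1 − Φ(1.96/√(1 + r²))]. At τ = 0.2 that is about 24% to 28% per item with no treatment effect on measurement.

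**Simulation with a fixed gap.** Assumed: 2,500 placebo and 10,000 active participants, D = 0.2, one item, latent trait known, two-sided 5% test, 200 runs.

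| f | Pooled, T = 0: week-6 rejection | Pooled, T = 0: baseline rejection | Pooled, T = 0.1: week-6 gap | Same, minus baseline gap |
|---|---|---|---|---|
| 0 | 3% | 3% | 0.10 | 0.10 |
| 0.25 | 80% | 77% | 0.15 | 0.10 |
| 0.50 | 100% | 100% | 0.20 | 0.10 |
| 0.75 | 100% | 100% | 0.25 | 0.10 |

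Restricted to placebo-controlled trials, week-6 rejection with T = 0 is 3% to 8% at every f. With T = 0.1 the estimated gap is about 0.10 and rejection is 98% to 100%.

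**The case against.** The strongest reply is that the all-trials reading of the week-6 test is inferred. Table 1 ties active-comparator data to the baseline model, placebo is the primary comparison, and pooling may mean pooling over arms, as it explicitly does for baseline in the network section. If the week-6 set were placebo-controlled trials only, f would be 0. The article is also condensed and points to other publications for its methods. This lowers certainty but does not remove the point: the text names the sample and the contrast, states no restriction, and tests active classes too. Pooling over arms does not exclude trials without placebo.

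A reader might infer that the test compares different trial populations in place of randomised arms and can say nothing about treatment. The documents do not support that. The active group still contains the randomised counterparts of every placebo participant, so the contrast is a mixture.

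A reader might also infer that the baseline arm test is a mistake to be dropped. Before treatment, non-invariance in the pool signals trial mix, which makes the test a useful negative control; in the additive simulation, subtracting the baseline gap recovered the true shift. The protocol does not say it will be used this way, and "within the best-fitting baseline model(s") could refer to the model's structure rather than baseline data.

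Third, no stated rule makes Models 3a or 6a depend on arm invariance. Stage 1 results are to be discussed descriptively, and the explicit follow-up to a violation is illustrated or stated for sex. That stands and limits the consequence to interpretation.

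Finally, the gaps of 0.03 to 0.05 item SDs in the random-variation calculation are small, and the article lists fit indices, not a significance test. The Limitations section also concedes that trial heterogeneity may affect the psychometric models. These points temper the size. They do not supply a within-trial comparison.

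**Conclusion.** The point holds in a limited form. On the natural reading, the placebo-active and active-class invariance tests leave arm partly confounded with trial population, so the week-6 result alone cannot be attributed to treatment.

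The extent is unknown, because it depends on the share of active participants from trials without placebo and on how far item behaviour differs between trials. The estimate of 1.3 to 1.5 sampling standard errors (0.7 to 2.3 over the wider range) rests wholly on the assumed trial mix, allocation, split and between-trial SD. It should be read as showing that the problem can be material, not that it is. The effect is on how Models 3a and 6a are interpreted. A concrete and inexpensive method avoids the confounding, so the change is worth making.

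**What to change.** Amend the two invariance statements in the factor-analytic section:

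- Run the week-6 placebo-active test only in trials that randomised to both, with trial held fixed, for example by centring items within trial or adding trial indicators. Restriction alone is not quite enough, because allocation ratios that differ between trials can leave some confounding.
- Test active classes only in trials that randomised between them.
- Keep any baseline arm-invariance test, state that it uses baseline data, label it a negative control for trial mix, and read the week-6 result against it.
- Report how many trials and participants enter each contrast.

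The measurement model itself can still be estimated in the full pool.

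The cost is a few sentences, a filter on trials and fewer active participants in the test. Under the assumptions above, about 1,000 to 2,350 placebo and 2,000 to 4,700 active participants remain in the confirmatory half. Dropout by week 6 and separate analysis of PANSS and BPRS would reduce these further. Active-class contrasts may rest on few trials.
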